## INTRODUCTION

### Background

ST-segment elevation myocardial infarction (STEMI) is a life threatening, time-sensitive condition consisting of a sudden complete blockage of a coronary artery. It requires treatment within 30-90 minutes, and the diagnosis is made via electrocardiogram (ECG). Patients suspected of STEMI are referred to an emergency department (ED) for rapid evaluation, diagnosis, and treatment. Guidelines recommend the diagnosis be made within 10 minutes of arrival. However, the first 10 minutes of an ED visit typically consist of registration and triage. The median door-to-doctor time for an ED patient is 60 minutes. As a result, ED registration and triage staff use screening criteria to identify patients who should receive an early ECG to identify STEMI. To date, the test characteristics of the screening process have not been extensively investigated. This study will examine whether there is variation in STEMI screening performance in different EDs, and whether variability is associated with the comprehensiveness of the screening criteria used.

Chest pain is the classic symptom for STEMI, however 20-30% of STEMI patients do not report chest pain. Appropriately comprehensive STEMI screening criteria, used to trigger an early ECG (trigger criteria), should include more information than chest pain presence or absence. Ideal STEMI case capture occurs when trigger criteria also includes atypical symptoms like shortness of breath and dizziness; associated symptoms like jaw pain, neck pain or back pain; and considerations of the patient's age. Previously collected data suggest the inclusion of these characteristics in different EDs trigger criteria varies significantly. We hypothesize there is variability in the screening processes between institutions, and this variability is associated with different diagnostic test characteristics.

### Rationale

The ECG is often referred to as the screening test for STEMI. This is because 30-50% of patients with STEMI on ECG will not have an occlusive coronary artery thrombus when evaluated with coronary artery angiography, the criterion (gold) standard diagnostic test. Despite this limitation, the risk-benefit balance of early treatment verses further testing weighs in favor of early treatment. As a result, treatment is initiated based on the *reference diagnostic testing standard*, an ECG demonstrating STEMI. In the context of ED operations and patient flow, the trigger criteria is the

true screening test. Patients, who do not receive an early ECG from registration or triage, go on to receive typical ED care. This provides an opportunity to identify cases missed by the index test, making typical ED care an *alternative reference standard* for trigger negative patients.

We have looked at the STEMI screening performance at Vanderbilt University (Table S1). In doing so we considered a patient meeting trigger criteria, which prompts the ED registration or triage staff to initiate an early ECG, as a positive *index test*, and an ECG indicating STEMI as a positive *reference test*. We found that the screening process has high sensitivity and negative predictive value with poor positive predictive value and limited specificity. The likelihood ratio of positive test is 5.2 (probability of a person with a STEMI ECG screening positive via screening trigger criteria), and that of a negative test is 0.025 (probability of a person with a STEMI ECG not being identified with screening trigger criteria). This study seeks to understand these local results in the context of broader clinical practice and variability of trigger criteria between institutions.

### **Study Objectives**

This study has two objectives. It will first examine whether the STEMI screening performance observed at Vanderbilt is generalizable. We will do this by calculating 2x2 contingency table data for patients seen in six additional EDs (in different regions of the country) individually, and then as a total population combined with Vanderbilt. Second, it will determine whether STEMI screening performance improves with more data incorporated into the trigger criteria by identifying whether there is an association between positive and negative likelihood ratios with the inclusion of associated symptoms, atypical symptoms, and age in the trigger criteria.

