### **Potential Risks and Benefits**

The ED is the unit of observation in this study. As a result, the data consists of aggregate numbers representing ED patient care events in 2014. Protected health information (PHI) and patient level data may be reviewed within the local ED to get the aggregate numbers we will use to calculate screening performance. Related data extraction will use the administrative reporting functions within the hospitals' electronic medical record systems (EMR) and review of existing summative data reports from the hospitals' STEMI case review committees. As a result there is limited potential for study-related breaches in PHI confidentiality, thus presenting minimal risk to the EDs and their patients. The participating EDs are involved in this study as a quality improvement effort with the intent to publish the results as research. The benefit to the EDs, and the patients they serve, is gaining knowledge about their local practice in the context of national peers to inform their current clinical STEMI screening practices. There is no compensation for participation.

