### **SAMPLE SIZE**

Seven EDs will be included. In 2014 these EDs saw 64353, 59929, 53165, 155000, 68621, 46378, 60000 patients. This results in a total of 507446 patients screened for STEMI. Based on previously reported data, and Vanderbilt's 2014 data, the incidence of STEMI is approximately 0.14-0.18%. Using the median estimate of 0.16% we anticipate 812 STEMI cases.

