### **FINAL ANALYSIS PLAN**

Two-by-two contingency tables will be calculated for each ED, and all EDs combined (Table S2). The data will be reported as sensitivity, specificity, negative predictive value, positive predictive value, false negative rate, false positive rate, likelihood ratio of being screened for an early ECG (positive index test) if the ECG demonstrates STEMI (positive reference test), likelihood ratio of being screened for an early ECG (positive index test) if the ECG does not show STEMI (negative reference test). This data will then be correlated with the inclusion of atypical symptoms, associated symptoms or age (representing yes or no as binary values) in the trigger criteria via a multi-variate logistic regression to see if there is an association.

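### Generalizability and between-ED variation are to be read from separate ED tables and a crude total that includes Vanderbilt, a method that cannot separate real differences in sensitivity from chance

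*Protocol*

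**What the plan says.** The protocol sets two related questions. The Background says: "This study will examine whether there is variation in STEMI screening performance in different EDs". The Study Objectives say: "It will first examine whether the STEMI screening performance observed at Vanderbilt is generalizable".

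The method for the second question follows in the same section. Tables are to be calculated for six additional EDs "individually, and then as a total population combined with Vanderbilt". The Final Analysis Plan repeats this: "Two-by-two contingency tables will be calculated for each ED, and all EDs combined (Table S2"). The section on objectives and outcome measures likewise lists the performance measures from these tables for seven EDs. The only further step is a regression on the content of the trigger criteria, which serves Objective 2.

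Under Potential Risks and Benefits the protocol states: "The ED is the unit of observation in this study". The document names no total without Vanderbilt, no measure of spread between EDs and no criterion for calling the Vanderbilt result generalizable.

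**The concern.** Two features of the stated method fit poorly with the two questions.

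First, the only aggregate named for setting Vanderbilt in context contains Vanderbilt, so any difference between Vanderbilt and the rest is shrunk towards zero.

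Second, STEMI is rare. The sensitivity of one ED rests on roughly a hundred cases, so seven sensitivities laid side by side will differ visibly even if the EDs perform identically. The Study Outcome section names the missed case rate as an outcome. A reader of seven tables could conclude that some EDs miss more STEMI than others, or that Vanderbilt is atypical, when the spread is only sampling error.

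**Working it through.** **Inputs.** From Sample Size: "In 2014 these EDs saw 64353, 59929, 53165, 155000, 68621, 46378, 60000 patients"; "the incidence of STEMI is approximately 0.14-0.18" per cent; "Using the median estimate of 0.16% we anticipate 812 STEMI cases". From Table S1 (Vanderbilt): 60 true positives and 15 false negatives among 75 STEMI cases, 55,454 true negatives among 68,546 without STEMI, 68,621 patients in all. The 68,621 in Sample Size is therefore Vanderbilt. Assumptions for illustration, not stated in the protocol: a common true sensitivity of 80% (the Table S1 value; 70% and 90% also shown) and a two-sided 5% level.

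**The protocol's own figures.** The seven volumes sum to 507,446, and 507,446 x 0.0016 = 811.9, which rounds to 812. Sensitivity is 60/75 = 80.0% and specificity 55,454/68,546 = 80.9%. All reproduce. The Wilson 95% interval for Vanderbilt's 80% is 69.6 to 87.5%.

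**Overlap.** Let w be Vanderbilt's share of the total, V its value and O the value in the other six EDs. Then V - [wV + (1 - w)O] = (1 - w)(V - O).

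- Share of patients: 68,621/507,446 = 13.5%.
- Share of STEMI cases: 75/812 = 9.2% with the observed count, or 110/812 = 13.5% with the count projected at 0.16%.
- A true 10-point difference appears as 0.908 x 10 = 9.1 points, or 0.865 x 10 = 8.6 points.

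**Chance spread in sensitivity.** Volume x 0.0016 gives about 103, 96, 85, 248, 110, 74 and 96 STEMI cases. The standard error at 80% is sqrt(0.16/n): 4.6 points at n = 74 and 2.5 points at n = 248. With 200,000 binomial simulations of seven EDs that share one true sensitivity, the gap between the highest and lowest observed value is:

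| Incidence | True sensitivity | Mean gap (points) | 95th percentile | Gap of 10 points or more |
|---|---|---|---|---|
| 0.16% | 80% | 10.8 | about 17 | 56% |
| 0.16% | 70% | 12.3 | 19.3 | 71% |
| 0.16% | 90% | 8.1 | 12.6 | 22% |
| 0.14% | 80% | 11.5 | 18.0 | 63% |
| 0.18% | 80% | 10.1 | 15.9 | 49% |
| 0.109% | 80% | 13.0 | 20.4 | 76% |

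The last row applies Vanderbilt's own Table S1 rate (75/68,621) to every ED. That is an assumption below the protocol's stated range.

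In the first row, with specificity held at 0.809, the median lowest and highest LR- are about 0.18 and 0.31.

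**Specificity.** The standard error is sqrt(0.81 x 0.19/n), with n close to the ED volume: 0.10 points for 155,000 patients and 0.18 points for 46,378. Chance spread is negligible.

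**What a comparison without overlap could show.** The other six EDs have 507,446 - 68,621 = 438,825 patients, or about 702 STEMI cases at 0.16%. With both groups at 80%, the standard error of the difference is sqrt(0.16/75 + 0.16/702) = 4.9 points, so the 95% half-width is about 9.5 points. With Vanderbilt at 80%, power is 14% if the others are truly at 75%, 43% at 70%, 23% at 85% and 70% at 90%.

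**The case against.** The strongest defence is that this is a descriptive study whose outcomes are worded as estimates and a description, and that intervals and heterogeneity measures commonly stand in an analysis plan, which is not shown here. That is fair as far as it goes: missing ED-level intervals alone would not be a finding. What stands is the method the protocol itself fixes for Objective 1, which is separate tables and a total that includes Vanderbilt.

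A reader might infer several stronger things that the documents do not support.

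- *That the benchmark is simply compared with itself.* The six other EDs are also tabulated individually, Vanderbilt is at most about 14% of the total, and a total without it can be had by subtraction. No section says the seven-ED total is to be tested against Vanderbilt.
- *That the crude sum assumes one common sensitivity and so contradicts the hypothesis of variation.* It does not. It is a volume-weighted average over the patients seen, valid as description whether or not EDs differ. That one ED supplies 155,000/507,446 = 30.5% of it follows from averaging over patients.
- *That the combined estimate has error bars that are too narrow.* The protocol states no interval for it.
- *That all observed variation may be chance.* For specificity and false positive rate it would hardly be.

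A further fair point concerns remedies. With seven EDs, a bivariate random-effects model would be very imprecise, and a homogeneity test of specificity on tens of thousands of patients per ED would flag trivial differences. Neither should be required.

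**Conclusion.** The point holds in limited form. For sensitivity, false negative rate and LR-, the stated method cannot distinguish true variation between EDs from a chance gap that averages about 11 points (95th percentile about 17). This rests on an assumed common sensitivity of 80% and the protocol's 0.16% incidence. Over sensitivities of 70 to 90% at that incidence the mean gap runs from about 12 to 8 points, and at Vanderbilt's own lower rate it is about 13. Including Vanderbilt in the total is a lesser fault that shrinks a true difference by about a tenth. The comparison of Vanderbilt with the rest is weak in any case, because Vanderbilt contributes only 75 STEMI cases. The finding does not extend to specificity or false positive rate, and it does not make the seven-ED sum invalid as description.

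**What to change.** Change Study Objectives and Final Analysis Plan as follows.

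1. Use the six other EDs, Vanderbilt left out, as the comparator for Vanderbilt. Report the difference with a confidence interval, and state that a non-significant result will not be read as evidence of generalizability, since power is only about 14 to 43% if the others are truly 5 to 10 points lower.
2. Report each ED's sensitivity and LR- with confidence intervals, and a between-ED heterogeneity estimate for sensitivity, for example from a univariate random-effects logit model. If its prediction interval is used to place Vanderbilt, fit the model without Vanderbilt. Say that the estimate is imprecise with so few EDs. For specificity, report the size of the differences between EDs rather than a test.
3. Keep the seven-ED sum, labelled as a volume-weighted descriptive table.

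No new data are needed. The cost is a little more analysis of the same tables, and wider stated uncertainty.

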### **Potential Risks and Benefits**

The ED is the unit of observation in this study. As a result, the data consists of aggregate numbers representing ED patient care events in 2014. Protected health information (PHI) and patient level data may be reviewed within the local ED to get the aggregate numbers we will use to calculate screening performance. Related data extraction will use the administrative reporting functions within the hospitals' electronic medical record systems (EMR) and review of existing summative data reports from the hospitals' STEMI case review committees. As a result there is limited potential for study-related breaches in PHI confidentiality, thus presenting minimal risk to the EDs and their patients. The participating EDs are involved in this study as a quality improvement effort with the intent to publish the results as research. The benefit to the EDs, and the patients they serve, is gaining knowledge about their local practice in the context of national peers to inform their current clinical STEMI screening practices. There is no compensation for participation.

### **OBJECTIVES AND OUTCOME MEASURES**

This study will see whether the Vanderbilt results are generalizable by calculating 2x2 table data (see Table 1) for 7 EDs in different regions of the United States. Specifically, we will identify the sensitivity, specificity, negative predictive value, positive predictive value, false negative rate, false positive rate, likelihood ratio of being screened for an early ECG if the patient's ECG shows STEMI, likelihood ratio of triggering an early ECG if the patient's ECG is negative.

### **STUDY DESIGN**

#### **Design**

Cross sectional, retrospective cohort, multi-centered study

#### **Subject Inclusion**

All patients screened for an early ECG to identify STEMI in 2014 in seven different EDs

#### **Data Collection**

A site-PI from each ED will be responsible for extracting aggregate figures included in the study survey (Appendix I) using data from their EMR reporting functions and their hospital STEMI case review committee. To reduce misclassification bias, STEMI is defined using ICD-9 codes previously validated in the literature (410.01, 410.11, 410.21, 410.31, 410.41, 410.51, 410.61, 410.81, 410.91). The EMR will provide aggregated numbers on ED care events (number of patients seen, number of patients receiving an early ECG as a result of triggering the screening criteria, etc.), while the hospital STEMI committee report will provide verifying counts for all ED STEMI cases, whether the early ECG demonstrated STEMI, and missed ED STEMI cases. For any discrepancies between the EMR and STEMI committee reports, the site PI will review the associated patient charts and make a clinical decision on whether the case was Trigger positive or negative, and STEMI positive or negative. The survey is included as appendix I, and will be sent to the site-PIs via email using REDCap. REDCap will also serve as a secure study data repository. The questionnaire has been reviewed by a biostatistician for completeness and to ensure it appropriately supports the planned analysis. (see attached)

### **Study Timeline**

The study will begin upon receipt of IRB approval from all participating sites. We anticipate data collection will take four weeks. Analysis will begin upon receipt of data from all participating sites. The data will be analyzed with the assistance of the Department of Biostatistics at Vanderbilt.

### **Enrollment**

Sites will be enrolled upon the submission of a completed survey and institutional IRB approval letter.

### **Confidentiality and Source Data**

Only key study personnel at the Data Coordinating Center, Vanderbilt University, will have access to the study data from all 7 EDs.

### **SAMPLE SIZE**

Seven EDs will be included. In 2014 these EDs saw 64353, 59929, 53165, 155000, 68621, 46378, 60000 patients. This results in a total of 507446 patients screened for STEMI. Based on previously reported data, and Vanderbilt's 2014 data, the incidence of STEMI is approximately 0.14-0.18%. Using the median estimate of 0.16% we anticipate 812 STEMI cases.

### **FINAL ANALYSIS PLAN**

Two-by-two contingency tables will be calculated for each ED, and all EDs combined (Table S2). The data will be reported as sensitivity, specificity, negative predictive value, positive predictive value, false negative rate, false positive rate, likelihood ratio of being screened for an early ECG (positive index test) if the ECG demonstrates STEMI (positive reference test), likelihood ratio of being screened for an early ECG (positive index test) if the ECG does not show STEMI (negative reference test). This data will then be correlated with the inclusion of atypical symptoms, associated symptoms or age (representing yes or no as binary values) in the trigger criteria via a multi-variate logistic regression to see if there is an association.

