### **STUDY OUTCOME**

- Estimates for the screening performance of ED trigger criterion for an early ECG to identify STEMI including sensitivity, specificity, NPV, PPV, LR+, LR-, and the missed case rate (false negative rate)
- Description of whether the comprehensiveness of the criteria influences screening performance.

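### The final analysis plan lets PPV and NPV, which move with each ED's STEMI incidence, into an association analysis that the objectives limit to the likelihood ratios

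*Protocol*

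**What the plan says.** Three parts of the protocol define what is compared with the content of the trigger criteria, and they do not agree.

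- **Study Objectives.** The second objective is met by "identifying whether there is an association between positive and negative likelihood ratios with the inclusion of associated symptoms, atypical symptoms, and age". Only LR+ and LR- are named.
- **Final Analysis Plan.** "The data will be reported as sensitivity, specificity, negative predictive value, positive predictive value, false negative rate, false positive rate", followed by two likelihood ratios. The next sentence reads "This data will then be correlated with the inclusion of atypical symptoms, associated symptoms or age", to be done "via a multi-variate logistic regression to see if there is an association". The only antecedent is the whole list. PPV and NPV are not excluded, and no adjustment for incidence is mentioned.
- **Study Outcome.** Screening performance is described as "including sensitivity, specificity, NPV, PPV, LR+, LR-, and the missed case rate (false negative rate", and the second outcome asks whether the comprehensiveness of the criteria influences that performance.

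Two other statements matter. Under Potential Risks and Benefits: "The ED is the unit of observation in this study". Under Sample Size: "the incidence of STEMI is approximately 0.14-0.18" percent.

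**The concern.** The second objective asks whether the trigger works better when its criteria cover more. LR+ and LR- are functions of sensitivity and specificity alone, so they suit that question. PPV and NPV also depend on how common STEMI is among an ED's patients. If they enter the regression, a difference in incidence between EDs that do and do not use, say, an age threshold would appear as an effect of the threshold. Because the Study Outcome section counts PPV and NPV as screening performance, such a result could be reported as evidence that comprehensiveness matters.

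**Working it through.** **Inputs.** Table S1: 60 true positives, 15 false negatives, 13,092 false positives, 55,454 true negatives. Sample Size: seven ED volumes, incidence 0.14-0.18%, and 0.16% as the working value.

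**The plan's own figure.** The volumes sum to 507,446, and 507,446 x 0.0016 = 811.9, which reproduces the stated 812.

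**Table S1 quantities.** Sensitivity = 60/75 = 0.800. Specificity = 55,454/68,546 = 0.809. Incidence = 75/68,621 = 0.109%. LR+ = 0.800/(1 - 0.809) = 4.19 and LR- = 0.200/0.809 = 0.247. (The Rationale gives 5.2 and 0.025. That is a separate discrepancy; the counts are used here.)

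**Dependence on incidence.** With incidence p:

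- PPV/(1 - PPV) = LR+ x p/(1 - p)
- (1 - NPV)/NPV = LR- x p/(1 - p)

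On the log-odds scale, a difference between EDs in PPV or in 1 - NPV is the difference in log LR plus the difference in log-odds of incidence. The second term has nothing to do with the trigger. With sensitivity and specificity held at the Table S1 values:

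| Incidence | PPV | Missed STEMI per 10,000 trigger-negative (1 - NPV) |
|---|---|---|
| 0.109% | 0.456% | 2.70 |
| 0.14% | 0.584% | 3.46 |
| 0.16% | 0.667% | 3.96 |
| 0.18% | 0.750% | 4.46 |

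PPV changes by a factor of 0.750/0.456 = 1.64 over the full range and by 0.750/0.584 = 1.28 from 0.14% to 0.18%. LR+ and LR- are the same in every row. From 0.14% to 0.18%, NPV itself moves only from 99.965% to 99.955%.

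**Effect on the test.** The protocol gives neither the form of the logistic regression nor an alpha, so both are assumed here (two-sided 0.05). The simulations used the seven stated volumes and identical true sensitivity and specificity everywhere, with 1,000 to 1,500 replicates per scenario.

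Grouped-binomial logistic regression, which treats patients as independent, gave these rejection rates per criterion:

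| Incidence across EDs | PPV | NPV |
|---|---|---|
| Equal, 0.16% | 4-7% | 4-6% |
| Random over 0.14-0.18%, unrelated to the criterion | 10-11% | 6% |
| Random over 0.109-0.18%, unrelated to the criterion | 22-24% | 9% |
| 0.14% v 0.18%, fully aligned with one criterion | 83-88% | 32-34% |

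NPV reacts less because it rests on fewer events. At 812 cases and 80% sensitivity, about 0.2 x 812 = 162 are missed and 650 are detected.

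ED-level regression of log-odds PPV on the three criteria (seven observations) rejected 5.4% of the time per criterion over 0.14-0.18% and 5.0% over 0.109-0.18%. Random variation in incidence does not inflate this test.

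**Does restricting the measures secure the level?** In the grouped-binomial runs sensitivity and specificity rejected about 4-6% of the time, but only because they were simulated as identical in all EDs. When specificity was allowed to differ between EDs by +/-1 percentage point, unrelated to the criteria, the same model rejected for specificity about 62-64% of the time per criterion.

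**The case against.** The strongest reply is that the Study Objectives already fix the right measures. On that view the Final Analysis Plan only has a loose back-reference, which a statistical analysis plan could tighten. It is true that the objective is sound and the fix merely restores it. But the section does state its scope, that scope is wider than the objective, and the Study Outcome section supports the wider reading. The protocol should not leave two answers.

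Four stronger readings are tempting, and the documents do not support them.

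- *The association test rejects whenever incidence differs between EDs.* The inflation under random variation belongs to a model that ignores between-ED variance. The protocol names the ED as the unit of observation, and an ED-level analysis keeps its level. Since the form of the regression is not given, neither model can be called the protocol's.
- *The protocol expects EDs to range over 0.14-0.18%.* The Sample Size section gives that range as an approximate overall incidence, takes its midpoint and applies it to the total. It is not a stated spread between EDs. Table S1 shows one ED at 0.109%, but a uniform spread from there to 0.18% is an assumption.
- *An ED that matches Vanderbilt's sensitivity and specificity would be judged a failure to reproduce its results.* No agreement rule for PPV is set, and the Rationale describes Vanderbilt's PPV only as poor, which fits both 0.46% and 0.75%.
- *PPV and NPV are equally affected.* NPV stays near nominal (6%) over 0.14-0.18% even under the grouped model.

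**Conclusion.** The point stands as a scope conflict: the Final Analysis Plan admits two incidence-dependent measures into an association analysis that the Study Objectives reserve for LR+ and LR-. The dependence follows from the definitions. At fixed Table S1 performance, PPV runs from 0.46% to 0.75% as incidence goes from 0.109% to 0.18%.

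How much harm follows depends on matters the protocol does not settle. If incidence differs systematically with the criteria, the bias is material, chiefly for PPV; nothing in the documents says that it does. If incidence varies at random, the PPV error rate rises to about 10-11% or 22-24% per criterion only under a patient-level grouped model and the assumed spreads, and stays near 5% at ED level. These rates assume a two-sided alpha of 0.05, the simulated incidence patterns, and sensitivity and specificity that do not themselves change with incidence. The likelihood-ratio regressions were not simulated.

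**What to change.** In the Final Analysis Plan, replace the open back-reference with a sentence that limits the criteria-association analysis to LR+ and LR-, and the sensitivity and specificity from which they derive, in line with the Study Objectives. Report PPV and NPV for each ED descriptively beside that ED's STEMI incidence (survey question 8 divided by question 6), or standardise them to one common incidence such as 0.16%. Do not use the raw values to judge association with the criteria. Word the Study Outcome section to match.

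The cost is one sentence and two fewer measures in the association analysis; no new data are needed. The change removes the dependence on incidence. It does not by itself guarantee the error rate, so the form of the regression still has to allow for variation between EDs.

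### The Final Analysis Plan relates all listed accuracy measures, including prevalence-dependent PPV and NPV, to three trigger elements, while Study Objectives judges Objective 2 by LR+ and LR- only, and no deciding test of comprehensiveness is named

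*Protocol*

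**What the plan says.** Three sections of the protocol describe the second objective, and they differ.

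- **Study Objectives** asks "whether STEMI screening performance improves with more data incorporated into the trigger criteria". It says how this will be judged: by the "association between positive and negative likelihood ratios with the inclusion of associated symptoms, atypical symptoms, and age in the trigger criteria". That is two measures against three elements.
- **Final Analysis Plan** first lists eight measures: "The data will be reported as sensitivity, specificity, negative predictive value, positive predictive value, false negative rate, false positive rate", followed by two likelihood ratios. It continues: "This data will then be correlated with the inclusion of atypical symptoms, associated symptoms or age (representing yes or no as binary values", to be done "via a multi-variate logistic regression to see if there is an association".
- **Study Outcome** promises a "Description of whether the comprehensiveness of the criteria influences screening performance". This is one exposure, with no measure named for the comparison.

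The section on potential risks and benefits adds that "The ED is the unit of observation in this study", and Sample Size fixes the number of EDs at seven. The protocol gives no significance level, no primary measure for Objective 2, and no score or joint test that represents comprehensiveness.

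**The concern.** The analysis section is wider than the objective it serves. Its subject is most naturally the list of measures in the sentence before it, so each of them is set against each of the three elements. This has two consequences.

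First, with only seven EDs, more associations examined means more chances that one stands out with no real effect behind it. Nothing in the text says which one would answer the question about comprehensiveness.

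Second, PPV and NPV depend on how common STEMI is at each ED as well as on the trigger criteria. If prevalence happens to differ between EDs that include an element and EDs that do not, a case-mix difference can be reported as an effect of the criteria. With seven EDs such an alignment can easily arise by chance.

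**Working it through.** **1. The plan's own figures.** The seven ED volumes in Sample Size sum to 64,353 + 59,929 + 53,165 + 155,000 + 68,621 + 46,378 + 60,000 = 507,446. Times 0.0016 this gives 811.9, so the stated 812 STEMI cases reproduce. The protocol states no error rate to reproduce.

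**2. Number of associations.**
- Study Objectives: 2 measures × 3 elements = 6.
- Final Analysis Plan: 8 × 3 = 24. The false negative rate is 1 − sensitivity and the false positive rate is 1 − specificity, so six measures are distinct: 6 × 3 = 18.

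**3. PPV and NPV with identical criteria.** Take sensitivity 0.80 and specificity 0.81 (Table S1) and the incidence range 0.14-0.18% (Sample Size). PPV = Se·p / [Se·p + (1 − Sp)(1 − p)].
- p = 0.0014: 0.00112 / (0.00112 + 0.19 × 0.9986) = 0.00112 / 0.19085 = 0.59%.
- p = 0.0018: 0.00144 / (0.00144 + 0.19 × 0.9982) = 0.00144 / 0.19110 = 0.75%.

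This is a relative change of 28%. Table S1 shows that one site lies outside the range: prevalence 75/68,621 = 0.109% and PPV 60/13,152 = 0.46%. Likewise 1 − NPV = (1 − Se)p / [(1 − Se)p + Sp(1 − p)] moves from 0.00028/0.80915 = 0.035% to 0.00036/0.80890 = 0.045%.

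**4. Chance of at least one spurious association.** Two-sided 0.05 is an assumption.

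If the tests were independent, the chance is 1 − 0.95^k: 26.5% for k = 6, 60.3% for k = 18 and 70.8% for k = 24. The measures are correlated, so these figures are too high.

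A null simulation allows for the correlation. It used seven EDs with the stated volumes, Table S1 sensitivity and specificity, and elements unrelated to performance. Each distinct measure was regressed linearly on the three elements at ED level, leaving 7 − 4 = 3 residual degrees of freedom. Two sets of settings were run:

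| Prevalence | Between-ED SD (logit) | 18 associations | LR+ and LR- only (6) |
|---|---|---|---|
| 0.16% | 0-0.4 | 33-38% | 14-19% |
| about 0.135% | 0-0.5 | 34-40% | 14-20% |

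The second prevalence is slightly below the protocol's range, with little effect on the result. In the second set, one measure against three elements gave about 11%, and one measure against a 0-3 element count gave about 5%.

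**5. Sensitivity to the model.** If the logistic regression were run on pooled patient counts for sensitivity and specificity, ignoring ED clustering, the chance of at least one of its six coefficients reaching p < 0.05 was 23% with no between-ED variation. It was 97% or more once the between-ED SD was 0.05 or larger. Even a single contrast (missed-case rate on a 0-3 score) gave 5%, 15%, 34% and 40% at SDs of 0, 0.2, 0.4 and 0.5 under that model.

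**6. Information available.** Three separate elements leave 3 residual degrees of freedom (critical t 3.18). One score leaves 7 − 2 = 5 (critical t 2.57).

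**The case against.** Several points on the other side stand.

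- **No decision rule is stated.** A reader might infer that any one positive result counts as success, or that a stated error rate is breached. The documents support neither: there is no significance level or success criterion, and Study Outcome calls the product a description. The risk is over-reading an association.
- **The three elements are not in conflict.** A reader might infer that using separate elements contradicts the objective. Study Objectives itself expresses more data as these same three elements. The mismatch lies in the measures, and in the lack of any test that represents comprehensiveness as a whole.
- **The count depends on the reading.** The sentence could refer to the underlying 2x2 counts. A logistic model for sensitivity and specificity would then give six coefficients. This is possible but less natural, and it still would not match the likelihood ratios that Study Objectives names.
- **The percentages come from a model the protocol does not specify.** This is correct, and they must be labelled so.
- **Primary contrasts and exploratory labels are often left to an analysis plan.** That is true of detail. Here, though, the protocol itself fixes outcomes, predictors and model, and what it fixes is wider than its own objective.

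**Conclusion.** The point holds as an inconsistency in stated text. Study Objectives judges Objective 2 by six associations, the Final Analysis Plan on its natural reading examines 18 distinct ones, and Study Outcome speaks of one exposure that no specified test represents. The clearest harm is the inclusion of PPV and NPV: a 28% relative shift in PPV follows from the protocol's own incidence range with no difference in criteria.

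Under an assumed two-sided 0.05 and an ED-level linear regression on seven EDs, widening the set raises the chance of at least one spurious association from 14-20% to 33-40%, roughly one in three. It would be too strong to call a chance finding likely, since the figure is below one half. It would also be wrong to read the figure as describing the planned logistic regression. A pooled version that ignores ED clustering has a larger error once EDs vary, and one contrast holds its nominal level only if analysed at ED level.

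**What to change.** Revise the Final Analysis Plan as follows.

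1. Confine the association analysis to LR+ and LR-, the measures that Study Objectives names. Report PPV and NPV descriptively only. Drop the false negative and false positive rates as separate outcomes of that analysis, since they are complements of sensitivity and specificity; they can still be tabulated.
2. Name one deciding ED-level test of comprehensiveness, for example the count of added elements from survey question 5 (0-3) or a joint test of the three elements. State which measure is primary: testing both ratios at 0.05 would give up to 1 − 0.95² = 9.75% if they were independent.
3. State how sites with no established trigger criteria are handled, since question 5 offers that answer.
4. Report individual element effects as exploratory estimates with intervals.
5. Align Study Objectives, Final Analysis Plan and Study Outcome with this.

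The cost is wording only, with no new data. Single-element results lose confirmatory status, which seven EDs could hardly support, and a count weights the elements equally. The choice of score and primary measure remains with the sponsor. If a measure other than LR+ or LR- is preferred, Study Objectives has to change with it.
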